## Abstract

Despite evidence that exercise improves treatment outcomes, most people living with and beyond cancer (PLWBC) are insufficiently physically active. To address this challenge the Onco-Move Improvement of psychophysical fitness in adult cancer survivors pilot randomized controlled trial aims to investigate the 7-month effects of a 16-week supervised, multicomponent exercise programme on PLWBC adults aged 18–55. The study will include 40 participants currently undergoing cancer treatment or up to 5 years post-treatment with different types of cancer, who will be randomly assigned to the experimental or the control group. The exercise programme will take place three times a week for 16 weeks. We hypothesize that the Onco-Move exercise programme will improve participants’ quality of life, sexual function, and stress-response strategies, as well as their nutrition, physical functions, and body composition. We also expect to observe physiological changes related to the intervention influencing inflammation, metabolism, muscle adaptation, and cellular aging. The Onco-Move exercise programme, once validated, has the potential to be implemented in oncological non-governmental organizations (NGOs) and hospitals in Poland and Spain, among others, as a feasible, effective, and safe non-pharmacological aid for cancer patients and survivors.

## 1. Introduction

Cancer accounted for nearly 20 million new cases and 10 million deaths in 2022 [1]. Estimates suggest that approximately one in five men or women will develop cancer in their lifetime, whereas around one in nine men and one in twelve women will die from it [1]. The number of diagnoses is also increasing among younger adults [2]. One-fourth of new incidents in 2022 occurred among people aged 15–54, accounting for nearly 1.7 million deaths in this population [3]. Importantly, early-onset cancer (defined as cancer diagnosed before the age of 50) has been rising globally in recent decades. At the same time, the majority of published exercise oncology research has focused on older adults, leaving younger and middle-aged people living with and beyond cancer relatively underrepresented in clinical trials. Moreover, projections indicate that the global incidence and mortality of early-onset cancer are expected to increase by 31% and 21%, respectively, by 2030 [4].

Advanced medical treatments have significantly reduced mortality rates among cancer patients [5]. However, the majority of individuals living with and beyond cancer will experience compromised physical and cognitive function due to cancer treatments and side-effects [6]. Treatments such as chemotherapy, radiotherapy, immunotherapy, or surgery can have harmful side-effects that negatively impact quality of life [7]. Physical activity can be an answer to avoid or minimize some of these side-effects.

In the past, clinicians advised cancer patients to rest and to avoid physical activity, but early exercise research in the 1990s and 2000s challenged this advice [5]. Between 2010 and 2022, the American Cancer Society (ACS) and the American College of Sports Medicine (ACSM) published recommendations for physical exercise and nutrition for cancer survivors [5,8,9]. Similarly, in 2021, the World Health Organization (WHO) released guidelines asserting that physical activity can benefit individuals post-cancer treatment by reducing mortality from cancer and lowering the risk of recurrence or the emergence of a second primary cancer [10].

Despite evidence that exercise improves treatment outcomes, PLWBC do not follow these recommendations. A total of 36.7% of cancer survivors aged 18 years and older do not perform any physical activity [11], and up to 93% report insufficient physical activity in their leisure time [12]. Some contributing factors include a lack of time, motivation, and self-discipline and also a lack of personalized exercise programs [12].

To address these challenges, the Onco-Move pilot randomized controlled trial aims to investigate the 7-month effects of a 16-week supervised, multicomponent exercise programme on adults aged 18–55 living with or beyond cancer. The results of this study may help to assess the effectiveness of exercise as a therapeutic component of health-related quality of life (HRQoL), functional fitness, body composition, nutrition, and other factors described later in this publication.

Although no dietary intervention will be implemented, nutrition is considered a core lifestyle dimension within the Onco-Move study. Adherence to the Mediterranean diet will be systematically assessed using the validated MEDAS questionnaire, not only as a control variable but also as a relevant lifestyle factor that may interact with exercise-related adaptations in PLWBC. This feasibility-oriented, observational approach allows for the exploration of diet–exercise interactions in real-world conditions, providing preliminary insight to inform future combined exercise–nutrition interventions.

## 2. Materials and Methods

### 2.1. Study Design and Protocol Registration

The Onco-Move pilot project is a parallel two-arm randomized controlled trial (RCT). The research aims to gain knowledge about a 16-week multicomponent in-person exercise programme and to investigate the extent to which it supports PLWBC, aged 18–55, both psychologically and functionally during the treatment process and after its completion, as well as whether it has an impact on long-term effects. The intervention is reported according to the Consensus on Exercise Reporting Template (CERT).

The study was registered at www.clinicaltrials.gov (NCT07087652) on 28 July 2025, before the enrolment of participants. The design of the project and the study protocol follow the CONSORT 2025 reporting guidelines [13].

### 2.2. Study Setting

Gdansk University of Physical Education and Sport (GUPES), Poland, will be responsible for the coordination and delivery of the Onco-Move project, which is co-designed in cooperation with the MOVE-IT Research group from the University of Cádiz, Spain. The research, intervention and monitoring will take place at GUPES.

### 2.3. Study Design

The project timeline is presented in Figure 1.

### 2.4. Recruitment

Recruitment will be supported by oncological foundations and associations from the Pomeranian Voivodeship and the University Clinical Center in Gdansk. A social media campaign will be implemented, and a project website will be published: https://onkotrening.pl/onco-move/ (accessed on 13 October 2025). Moreover, the project brochure will be distributed in hospitals and to oncological NGOs.

### 2.5. Eligibility Criteria

The participants’ inclusion and exclusion criteria are listed in Table 1.

In the case of pregnant women who wish to participate in the project, they will not be enrolled in the intervention but will be allowed to attend a free educational lecture on the WHO and ACSM guidelines for recommended physical activity for cancer patients.

### 2.6. Sample Size

The study was pragmatically powered with n = 20 participants per group (intervention and control) for this initial feasibility and estimation phase. The calculation assumes a two-sided α = 0.05 and a nominal power of 80%, using an ANCOVA model adjusted for baseline values and repeated measures to increase statistical efficiency. Previous exercise-based trials in PLWBC [14,15,16] have reported between-group differences of approximately 8–10 points in the EORTC QLQ-C30 Global Health Status/QoL domain, with standard deviations around 20–30 points. Based on these data, a fully powered confirmatory trial would require substantially larger samples; therefore, the present study adopts a realistic initial sample size aimed at (i) quantifying the signal of efficacy and its heterogeneity across subgroups, (ii) evaluating feasibility, adherence, and safety, and (iii) providing empirical estimates of variance, correlation, and attrition rates to inform a subsequent definitive trial with higher precision. Should recruitment capacity allow, the sample may be progressively expanded to narrow confidence intervals around clinically meaningful differences of 8–10 points.

Furthermore, feasibility expectations regarding adherence and dropout are informed by a previous pilot study conducted in 2023 at GUPES. Based on this experience, we anticipate an adherence rate of approximately 60–70% in the current RCT, with an expected dropout rate of around 25%. Dropout is primarily anticipated among participants undergoing active cancer treatment, who may experience treatment-related side-effects or changes in medical status that prevent continued participation.

### 2.7. Randomization

Participants will be randomly allocated to either the experimental group (EG) or the control group (CG), with n = 20 participants per group. The random sequence will be computer-generated in blocks of four to ensure balanced allocation between groups throughout recruitment. The sequence will be generated by the project coordinator at the University of Cádiz (MOVE-IT Research Group, Spain), who is not involved in participant recruitment, assessment, or intervention delivery, thereby ensuring allocation concealment. Group assignments will be communicated to the local principal investigator, who will subsequently inform each participant of their allocation. This procedure minimizes selection bias and preserves blinding of outcome assessors and data analysts.

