### 2.8. Blinding

Due to the nature of the intervention, participants and exercise trainers cannot be blinded. The study will therefore adopt a single-blind design, in which outcome assessors and data analysts remain blinded to group allocation. The randomization sequence will be stored by an independent investigator not involved in assessments or analyses. Participants will be instructed not to disclose their allocation during assessments. This approach ensures methodological transparency while minimizing assessment bias.

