### 2.12. Interventions

The Onco-Move exercise intervention is planned according to the CERT. The programme is based on the Individualized and Progressive Health Model [36] (presented in Figure 3.: Onco-Move Individualized and Progressive Health Model) and will include different types of exercises covering all the fitness components (cardio, strengthening, balance, shaping exercises, and stretching). The Individualized and Progressive Health Model (IPS) is a conceptual framework described in a technical monograph [36] and grounded in established exercise prescription principles widely supported by peer-reviewed exercise oncology guidelines.

Participants will perform exercises without any equipment, whereas specific exercises will be performed with such equipment as sports rubber bands, sensory-motor discs, Pilates balls, dumbbells, and cycle ergometers.

All training sessions will be conducted in fitness studios and the gym at Gdansk University of Physical Education and Sport by four certified professional fitness instructors, who will be additionally trained by a certified cancer exercise specialist, and the entire exercise program will be supervised by an expert exercise physiologist with experience in exercise interventions. The in-person interventions will be provided to a group of 20 participants.

The instructors who will supervise exercise performance will correct exercise techniques, ensure the participants maintain the correct movement pattern, provide guidance, provide feedback, and modify exercises as required by a specific type of cancer and treatment.

Adherence will be measured by the percentage of the Onco-Move training sessions completed, defined as the number of the training sessions attended divided by the total number of the training sessions delivered. The reason for absence from training (caused by the treatment regimen, side-effects of treatment, infections, and other reasons) will be reported by patients completing the post-training assessment form (an online tool created by the research team on the Google Forms platform). This approach will allow for feasibility to be evaluated under real-world conditions and provides critical information on barriers that cannot be fully eliminated within the scope of the current study.

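### Fixed, published blocks of four make about a third of allocations deducible if allocation is sequential, so an independent list generator does not by itself ensure concealment

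*Protocol article*

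**What the plan says.** Section 2.7 of the protocol article sets the ratio and size: "Participants will be randomly allocated to either the experimental group (EG) or the control group (CG), with n = 20 participants per group". The method is: "The random sequence will be computer-generated in blocks of four to ensure balanced allocation between groups throughout recruitment". Four is the only block size given, and no stratification is described. The sequence comes from a coordinator in Cádiz "who is not involved in participant recruitment, assessment, or intervention delivery, thereby ensuring allocation concealment". The section continues: "Group assignments will be communicated to the local principal investigator, who will subsequently inform each participant of their allocation". It concludes: "This procedure minimizes selection bias and preserves blinding of outcome assessors and data analysts".

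Section 2.8 describes a single-blind design. Outcome assessors and data analysts are blinded, but "participants and exercise trainers cannot be blinded". On custody it says: "The randomization sequence will be stored by an independent investigator not involved in assessments or analyses". Separation of the custodian from assessment and analysis is stated; separation from recruitment is not.

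Section 2.2 places the research and the intervention at one institution. Section 2.12 adds: "The in-person interventions will be provided to a group of 20 participants".

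**The concern.** Concealment means that whoever decides on entry cannot know the next assignment when deciding. Keeping the list off site is necessary for this but not sufficient. With a constant block size that is known, and past assignments that are known, the end of every block can be worked out without seeing the list. Here the block size stands in a published article, and the local principal investigator receives the assignments. Each participant knows his or her own group, and trainers will know who attends the programme. Section 2.7 nevertheless infers concealment from the generator's independence alone.

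What is at stake is comparability of the groups. Some entry criteria in Table 1 involve judgement, such as inactivity since diagnosis and commitment to three sessions a week. Entry can also be brought forward or delayed. The sole primary outcome (section 2.10) is a self-reported questionnaire score, and there are only 20 people per group. The trial is meant to quantify a signal of efficacy and supply estimates for a definitive trial (section 2.6), so an avoidable source of imbalance would carry forward.

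**Working it through.** The plan gives no figure for predictability, so there is none to reproduce.

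**Inputs.** Block size 4, ratio 1:1, 20 per group (section 2.7). Hence 40/4 = 10 complete blocks, which give exactly 20:20.

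**Assumptions.** Assignments become known one at a time, and someone tracks them in order. The first is implied by the aim of balance during recruitment but not stated outright; the second is not stated.

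**Certain allocations.** A block holds two exercise (E) and two control (C) places in one of six equally likely orders: EECC, CCEE, ECEC, ECCE, CEEC, CECE. An allocation is certain once one group's two places are used up.
- 1st and 2nd: never certain.
- 3rd: certain only if the first two match, which happens in 2 of 6 orders, probability 1/3.
- 4th: always certain.

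Expected number per block = 1 + 1/3 = 4/3 = 1.33. As a share, (4/3)/4 = 1/3 = 33.3%. Over 10 blocks, 10 × 4/3 = 13.3 of 40. Each block gives one certain allocation (probability 2/3) or two (probability 1/3), so the total lies between 10 and 20, with SD √(10 × 1/3 × 2/3) = 1.5.

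**Best guess.** Suppose the observer always guesses the group with more places left in the block.
- 1st: 1/2.
- 2nd: 2/3.
- 3rd: 1/3 × 1 + 2/3 × 1/2 = 2/3.
- 4th: 1.

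Mean = (1/2 + 2/3 + 2/3 + 1)/4 = 17/24 = 70.8%, against 50% under full concealment.

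**Effect of varying the block size.** The sizes below are assumptions, since the plan gives only four. In 3,000 simulated sequences of 40, the observer knows the set of possible sizes and all past assignments.

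| Block sizes | Certain allocations | Best guess correct |
|---|---|---|
| 4 only (exact) | 33.3% | 70.8% |
| 4 or 6 | 5.6% | 68.9% |
| 2, 4 or 6 | 4.1% | 69.9% |
| 4, 6 or 8 | 2.2% | 67.6% |

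Varying the size removes most certain predictions but lowers the best-guess rate by only about 1 to 3 percentage points. It is therefore only part of a remedy. If consent, eligibility and baseline are complete for everyone before a single randomisation step, no entry decision remains to be influenced and predictability no longer matters.

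**The case against.** The strongest reply is that the third is conditional. It requires sequential release, a person who tracks the order, and influence by that person over who enters next. The article does not say when assignments reach the local principal investigator, or whether that person screens or enrols. Delivery to one group of 20 is compatible with enrolling a cohort and randomising it together, in which case the problem disappears. The mechanics of release are also the kind of detail an article leaves to the full protocol. All of this stands, and for that reason the missing mechanics are not the point. The point is the block size that is stated and the inference drawn from the generator's independence. Keeping blocks for balance during recruitment makes most sense if people are allocated as they enter.

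Three stronger readings are tempting but not supported.
- **That site staff in general will predict a third of allocations.** The text names one recipient of the assignments. Assessors and analysts are blinded, and nothing says that trainers recruit or know the order of entry.
- **That oncologist approval lets the site steer entry.** Section 2.12 requires written approval from the participant's own oncologist before enrolment. That is an outside check, and nothing suggests the oncologist knows the sequence.
- **That the result is biased towards benefit.** Predictability is not bias. The model in section 2.14 adjusts for baseline value, age, sex and treatment status, which would absorb part of any steering on baseline condition, though not on motivation. The article also puts estimation ahead of confirmatory inference.

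**Conclusion.** The point holds in conditional form. If allocation is sequential and someone tracks the order, fixed blocks of four make on average 13.3 of 40 allocations (33%) certain in advance, with a minimum of 10. An independent off-site generator does not prevent this. The stated procedure therefore does not by itself ensure allocation concealment or minimise selection bias.

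A reader might infer that concealment has failed or that the trial will favour exercise. The documents support neither: they do not say who enrols or when assignments are released, and the size and direction of any bias are unknown. If the whole cohort were in fact enrolled before one randomisation step, the concern would fall away, but the article does not say so.

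**What to change.** **Preferred.** Complete consent, eligibility checks and baseline assessment for the cohort, then randomise it in one step from Cádiz. This fits a programme delivered to a group of 20. Section 2.6 allows the sample to be expanded; in that case do the same for each recruitment wave.

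**If entry must be sequential.** Replace the fixed blocks of four with randomly varying block sizes not disclosed to site staff. The size of four is already public, so withholding it now would not help; the list has to change. Release each assignment only after enrolment is final and baseline is recorded. That last step is needed because varying blocks alone barely reduce best-guess success.

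**Wording.** Revise section 2.7 so that concealment rests on these steps and not on the generator's independence alone.

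**Cost.** One new list and a revised paragraph. One-step randomisation means later notification for early entrants and a longer gap from baseline to programme start. Varying blocks may leave a slight imbalance in group sizes. If some participants have already been allocated, the change can apply only to those still to enter.

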### 2.8. Blinding

Due to the nature of the intervention, participants and exercise trainers cannot be blinded. The study will therefore adopt a single-blind design, in which outcome assessors and data analysts remain blinded to group allocation. The randomization sequence will be stored by an independent investigator not involved in assessments or analyses. Participants will be instructed not to disclose their allocation during assessments. This approach ensures methodological transparency while minimizing assessment bias.

### 2.9. Assessment Protocol

Each patient who participates in the project will undergo four assessments over the course of the project: (1) a baseline assessment—before participating in the Onco-Move training programme; (2) 8 weeks after the programme begins; (3) 16 weeks after the programme begins; (4) 3 months after the completion of the Onco-Move intervention.

### 2.10. Outcomes

Given the pilot and feasibility-oriented design of the study, health-related quality of life (HRQoL) is defined as the sole primary outcome. All other outcomes, including functional, physiological, biochemical, genetic, and telomere-related measures, are considered secondary or exploratory and will be interpreted with an emphasis on estimation, feasibility, and hypothesis generation rather than confirmatory inference.

A graphical design of the outcomes measured is presented in Figure 2.

**a. Primary outcome**

*HRQOL* will be assessed pre-, during, and post-intervention and at follow-up using a validated questionnaire: EORTC QLQ-C30 [17]. This instrument measures general quality of life and includes multiple subscales (e.g., physical, emotional, cognitive functioning). Scores on each scale range from 0 to 100. For functional scales and global health status, higher scores indicate better functioning or QoL. For symptom scales, higher scores indicate more severe symptoms. The validated Polish version of the EORTC QLQ-C30 will be used. Data will be collected via digital or paper formats and analyzed.


We are aware that the assessment battery may be demanding. Therefore, all tests were carefully selected based on their clinical relevance and feasibility, and the total duration of each assessment session was evaluated in advance. The full testing protocol will be pilot-tested prior to study initiation, and the research team will be extensively trained to conduct all assessments as efficiently as possible in order to minimize participant fatigue and burden. Assessments will be scheduled with appropriate rest periods, and procedures may be adapted or postponed if participants experience excessive fatigue or treatment-related symptoms.

A summary of the time-point measurements is presented in Table 2.

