### 2.14. Statistical Analysis

Descriptive statistics will summarize baseline characteristics. Primary analyses will follow the intention-to-treat (ITT) principle. To evaluate changes across time points (baseline, 8 weeks, 16 weeks, follow-up), a mixed-effects model for repeated measures (MMRM) will be applied with random intercepts for participants and fixed effects for group, time, and group × time interaction, adjusting for relevant covariates (baseline value, age, sex, treatment status). A covariance structure such as compound symmetry or AR(1) will be selected based on model fit.

For outcomes with only two time points or in case of convergence limitations due to sample size, ANCOVA models adjusted for baseline values will be used as a complementary approach. Effect sizes (Hedges’ g) and 95% confidence intervals will be reported to prioritize estimation over strict hypothesis testing, in line with the feasibility nature of the study. Missing data will be handled using maximum likelihood estimation within the mixed-model framework, and complete-case or multiple-imputation sensitivity analyses will be performed when appropriate. Exploratory moderator analyses (e.g., treatment status, cancer type, adherence) will be reported descriptively. Data will be analyzed using IBM SPSS Statistics (version 29) and Stata (version 18). All tests will be two-sided with α = 0.05.

Given the pilot and feasibility-oriented nature of the study, formal correction for multiple comparisons is not planned. Secondary and exploratory outcomes will be interpreted with caution, emphasizing estimation, variability, and hypothesis generation rather than confirmatory statistical inference.

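### The rule allowing assessments to be postponed for fatigue or symptoms does not exempt the QLQ-C30, so the timing of the primary score can depend on how the participant feels

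*Protocol article*

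**What the plan says.** Section 2.10 states that "health-related quality of life (HRQoL) is defined as the sole primary outcome". The instrument is the EORTC QLQ-C30. Its description under Primary outcome includes symptom scales ("For symptom scales, higher scores indicate more severe symptoms") and gives the mode of collection: "Data will be collected via digital or paper formats and analyzed".

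Section 2.9 sets the post-baseline assessments at "2) 8 weeks after the programme begins; (3) 16 weeks after the programme begins; (4) 3 months after the completion" of the intervention. Section 2.14 takes these as the time axis of the analysis: "To evaluate changes across time points (baseline, 8 weeks, 16 weeks, follow-up), a mixed-effects model for repeated measures (MMRM) will be applied".

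The closing paragraph of section 2.10 begins "We are aware that the assessment battery may be demanding". After describing pilot testing, staff training and rest periods, it ends with the rule that "procedures may be adapted or postponed if participants experience excessive fatigue or treatment-related symptoms". It then points to Table 2, whose first row is the primary outcome. Section 2.12 adds that training and assessments all take place at one site.

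**The concern.** The trigger for postponement (fatigue, treatment-related symptoms) overlaps with what the primary instrument measures. Suppose a participant on treatment is due at week 16 and feels unwell. If the whole session is moved and the questionnaire moves with it, the QLQ-C30 is completed once symptoms have eased, and the value enters the model as week 16. The low score that belonged to that date is not missing; a higher one has replaced it. The maximum-likelihood handling of missing data in section 2.14 does not address this, because nothing is missing.

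The situation is foreseeable. Table 1 admits people under treatment, and section 2.6 expects side-effects to interrupt participation in that group. At stake is the level of the primary score in each arm and, if the arms are postponed at different rates, the estimated group difference. In the exercise arm a postponed week-16 form would also be completed after the programme had ended.

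**Working it through.** The plan gives no postponement rate and no figure of its own on this point, so there is nothing to reproduce. The check has two parts.

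**1. Does the rule reach the QLQ-C30?**

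- For: the paragraph closes the section on all outcomes, speaks of the assessment battery as a whole, and refers to Table 2, which lists the QLQ-C30 first. Section 2.12 ties assessments to one site without excepting questionnaires. Where the protocol wants to confine a restriction to one test it says so: participants unfit for isokinetic testing stay eligible for the other assessments.
- Against: the paragraph is about the burden of testing, and adapting a procedure or scheduling rest suits physical tests better than a form. The QLQ-C30 is digital or paper and is not expressly tied to the laboratory session.
- Result: the text permits the questionnaire to be postponed but does not say that it is.

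**2. How large could the effect be?**

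From the documents (section 2.6): a difference of interest of 8–10 points on Global Health Status/QoL, and an SD of 20–30.

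Assumed, not in the documents:

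- day-to-day variation within a person makes up a share w = 10–40% of the variance;
- the QLQ-C30 moves with the session;
- the fraction q of assessments with the lowest day-to-day state is postponed, once, to an independent day;
- the trigger is fully aligned with the score. This makes the figures upper values for a given q and w.

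Within-person SD = SD × √w. Lowest case: 20 × √0.10 = 6.32. Highest case: 30 × √0.40 = 18.97.

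Days above the cut-off contribute φ(z_q) standard deviations to the mean, where φ is the normal density and z_q the q-quantile. Replaced days contribute 0. So

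upward shift in the arm mean = φ(z_q) × within-person SD.

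A simulation at q = 20% gave 0.279, against 0.280 from the formula.

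| Postponed (q) | φ(z_q) | × 6.32 | × 18.97 |
|---|---|---|---|
| 5% | 0.103 | 0.7 | 2.0 |
| 10% | 0.175 | 1.1 | 3.3 |
| 20% | 0.280 | 1.8 | 5.3 |
| 30% | 0.348 | 2.2 | 6.6 |

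Bias in the group difference = difference between the two arms' shifts (unrounded densities used):

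- equal postponement: about 0;
- 20% against 10%: 0.1045 × 6.32 = 0.7 to 0.1045 × 18.97 = 2.0 points;
- 30% against 5%: 0.2446 × 6.32 = 1.5 to 0.2446 × 18.97 = 4.6 points.

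Against 8–10 points, the first unequal case is 0.7/10 = 7% to 2.0/8 = 25%. The second is 1.5/10 = 15% to 4.6/8 = 58%.

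**The case against.** The best counter-argument is that this turns an ambiguity into a defect. The rule is permissive, its setting is the strain of laboratory testing, and nothing states that the QLQ-C30 is moved. That stands in part. A reader might infer that the primary score is collected preferentially on good days; the documents do not support that, because they describe only a permission and give no rates.

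A reader might also infer that instructors, who see the exercise arm three times a week, would trigger postponements and so favour exercise. The documents give them no role in scheduling assessments, and section 2.12 has them monitor training sessions only. The rule itself is not arm-specific. An opposite route, with controls postponed more often because exercise relieves fatigue, is just as conjectural. Hence the sign is unknown, and equal rates leave the group difference essentially unbiased.

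The absence of visit windows from a condensed article is not a fault, and none is claimed. The section 2.9 times and the postponement rule do not contradict each other: one gives nominal dates, the other a safeguard against burden.

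Finally, postponement can retain data from unwell participants that would otherwise be lost, which matters with about 25% dropout expected. That stands, and it argues against a rigid deadline for the form. It does not argue for leaving the questionnaire under the same rule as the physical tests.

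**Conclusion.** The point holds in limited form. A stated rule allows assessments to be moved because of symptoms, does not except the sole primary outcome, and feeds an analysis at nominal times. As written, the primary score can be taken on a later, better day.

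Whether this happens, how often, and in which arm cannot be told from the documents. The ranges above depend on the assumed share of day-to-day variance, the assumed postponement rates, and a trigger that follows the score perfectly; a weaker link would give less. They show that a marked imbalance could matter against 8–10 points, not that a bias of that size is expected.

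This is a worthwhile, low-cost improvement to a pilot that emphasises estimation. It does not invalidate the design.

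**What to change.** In the closing paragraph of section 2.10:

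- Limit the postponement rule to the physical and laboratory tests, leaving its content for those tests unchanged.
- State that the QLQ-C30 and the other questionnaires are completed at the nominal time in both arms, on the digital form already planned, whether or not the laboratory session is postponed.
- State that a late form is accepted rather than lost.
- Record the actual date of each assessment and the reason for any postponement, and report both by arm. A sensitivity check on actual timing is then possible.

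The cost is a few sentences and two recorded items per assessment. The downside is that questionnaires and physical tests will sometimes fall on different days, which slightly loosens analyses relating the two.
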